#### 4.3 JUSTIFICATION FOR DOSE

The 15 µg/kg/day dose was chosen based on the results from the Phase II study in achondroplasia in which this dose was equally efficacious to the 30 µg/kg/day dose in the Phase II trial for achondroplasia. While it is possible that patients meeting our study inclusion criteria could respond even better to a higher dose such as the 30 µg/kg dose, we decided to start with the lowest previous effective dose as this is an initial exploratory proof of principle study.

#### 4.4 END OF STUDY DEFINITION

A participant is considered to have completed the study if he or she has completed all phases of the study including the last visit or the last scheduled procedure shown in the Schedule of Activities (SoA), Section 1.3.

The end of the study is defined as completion of the last visit or procedure shown in the SoA in the trial globally.

### 5 STUDY POPULATION

#### 5.1 INCLUSION CRITERIA

Inclusion and exclusion criteria will be pre-screened based on information provided by the referring clinician. All inclusion and exclusion criteria will then be verified at the screening visit and official screening laboratory studies will be performed as part of that visit. There will be no birth weight or length inclusion or exclusion criteria.

In order to be eligible to participate in this study, an individual must meet all of the following criteria:

1. Parent(s) or guardian(s) are willing and able to provide written, signed informed consent after the nature of the study has been explained and prior to performance of any research-related procedure. Also, subjects under the age of 18 are willing and able to provide assent (if required) after the nature of the study has been explained and prior to performance of any research-related procedure.
2. Stated willingness to comply with all study procedures and availability for the duration of the study
3. Age  $\geq 3$  years 0 days AND  $\leq 10$  years 364 days for males,  $\leq 9$  years 364 days for females
4. Pre-pubertal defined as Tanner Stage 1 breasts in females and testicular volumes  $\leq 3$  cc in males. This must be confirmed at the Day 1 visit prior to initiation of vosoritide.
5. Patient height  $\leq -2.25$  SDS. All height SDS values are calculated using the CDC growth charts/data tables.

6. Patients with pathogenic or likely pathogenic variants in genes known to cause the specific genetic subgroups of short stature listed below are eligible for inclusion in the study. Pathogenicity of variants will be classified as per the American College of Medical Genetics criteria with the exception of *ACAN* mutations as detailed below. Documentation of the presence of the variant must be obtained using a lab results report from a CLIA certified laboratory. Classification of the variant's pathogenicity status will be performed by the Children's National study team.
- A. CNP deficiency due to mutations in *NPPC* – Subjects with heterozygous or homozygous defects in *NPPC* are eligible.
  - B. Hypochondroplasia – Subjects with heterozygous variants in *FGFR3* gene associated with hypochondroplasia are eligible. Subjects with variants in *FGFR3* known to cause achondroplasia or thanatophoric dysplasia or SADDAN syndrome will be excluded.
  - C. Patients with heterozygous defects in *NPR2* are eligible. Patients with homozygous defects in *NPR2* will be excluded.
  - D. Rasopathy patients (including Noonan syndrome, Costello syndrome, Cardiofaciocutaneous syndrome, Neurofibromatosis Type 1) – This include patients with heterozygous variants in the following genes:
    - i. BRAF
    - ii. CBL
    - iii. HRAS
    - iv. KRAS
    - v. LZTR1
    - vi. MAP2K1
    - vii. MAP2K2
    - viii. MRAS
    - ix. NF1
    - x. NRAS
    - xi. PPP1CB
    - xii. PTPN11
    - xiii. RAF1
    - xiv. RRAS
    - xv. RIT1
    - xvi. SHOC2
    - xvii. SOS1
    - xviii. SOS2
  - E. Patients with *SHOX* deficiency – Patients with either heterozygous, compound heterozygous or homozygous defects in *SHOX* including patients with heterozygous or homozygous deletions of the *SHOX* regulatory region known to cause *SHOX* deficiency.
  - F. Patients with heterozygous defects in *ACAN* - Patients must be heterozygous for a mutation in the *ACAN* gene. As there are no validated *in vitro* assays that reliably assess an individual variant's effect on aggrecan function, for the purpose of this clinical trial a mutation in *ACAN* will be defined as:

- a. A heterozygous deletion of the entire gene or of  $\geq 1$  complete exons of the gene
  - b. Any truncating mutation including frameshift, nonsense, splice site mutations within 2 bases of the exon/intron boundary, and start loss variants
  - c. Any missense mutation which meets all of the following criteria:
    - i. It has an aggregate minor allele frequency less than  $1 \times 10^{-5}$  based on the gnomAD data (gnomad.broadinstitute.org)
    - ii. It is predicted to be damaging by BOTH Polyphen2 and SIFT
    - iii. It segregates with the short stature phenotype in available family members or is a *de novo* mutation
  - d. In-frame insertions or deletions of  $>1$  amino acid
  - e. In-frame insertions or deletions of 1 amino acid must meet the same criteria as missense mutations. For the prediction programs, Alanine will be substituted for the deleted amino acid.
7. Absence of growth hormone deficiency defined as an IGF-1 level above the lower limit of the normal range of the assay. The IGF-1 may be repeated during the 6 month observation period and prior to the Day 1 visit. If this repeat IGF-1 is above the lower limit of the normal range of the assay, then the subject is deemed eligible. If a patient has an IGF-1 level below the lower limit of the normal range of the assay, two growth hormone stimulation tests must be performed using the routine local protocols. Patients with a peak growth hormone level  $\geq 7$  ng/ml will be considered growth hormone sufficient and will be eligible for inclusion as per the Growth Hormone Research Society International consensus . If indicated based on IGF-1 level from the referring clinician, the growth hormone stimulation test must be done as part of routine clinical care prior to enrollment. The rationale for using an IGF-1 below the normal range as the cut-off for further evaluation for growth hormone deficiency is that in patients with a clear genetic explanation for their short stature, an IGF-1 level anywhere within the normal range would be considered reassuring and would not lead to a growth hormone stimulation test in a routine clinical setting.
8. The subject and their guardian must speak one of the 11 languages for which the QoLISSY survey (a quality of life survey for short stature) is available. These include: English, Spanish, German, Russian, Swedish, Flemish, Italian, Turkish, French, Japanese, and Ukrainian.

Extension Phase Inclusion Criteria:

1. Subject completed all visits for the initial 18 months of the study.
2. Parent(s) or guardian(s) are willing and able to provide written, signed informed consent for the extension phase after the nature of the study has been explained and prior to performance of any research-related procedure. Also, subjects under the age of 18 are willing and able to provide assent (if required) after the nature of the study has been explained and prior to performance of any research-related procedure.
3. Subject must have a positive response to the first year of vosoritide therapy which is defined as:
  - For subjects with hypochondroplasia or *ACAN* mutations – A positive response is defined as an increase in annualized growth velocity of 1.6 cm/year when comparing 6-month observation period to initial 12 months of vosoritide treatment. This criterion is based on the adjusted mean response of patients with achondroplasia in the Phase III trial of

vosoritide which is a clinically significant response. ACAN patients can also have disproportion and are included in this category.

- For subjects with Rasopathies, *SHOX* mutations, *NPR2* mutations or *CNP* deficiency - A positive response is defined as an increase in annualized growth velocity of 3 cm/year when comparing 6-month observation period to initial 12 months of vosoritide treatment. This higher response criterion is due to growth hormone being approved for *SHOX* deficiency, Noonan syndrome, and for idiopathic short stature which could encompass *NPR2* mutations and *CNP* deficiency. In these types of patients, an increase in annualized growth velocity of 3 cm/year is more typical for patients treated with growth hormone, and thus, we want to ensure that patients treated with vosoritide have a similarly favorable response. However, if a subject has previously been treated with growth hormone and it was discontinued due to a poor response, if the increase in annualized growth velocity on vosoritide is greater than it was for growth hormone but still less than 3 cm/year, the subject can continue on vosoritide in the extension phase.
- 4. There are no inclusion criteria based on height or pubertal status for the extension phase of the protocol. Subjects may continue into the extension phase regardless of their height or pubertal status as the 12 Month Visit.

## 5.2 EXCLUSION CRITERIA

An individual who meets any of the following criteria will be excluded from participation in this study:

1. Growth plate fusion – Defined as a bone age via the Greulich and Pyle method of 13 years in females and 15 years in males. These patients have limited remaining growth potential.
2. Concomitant treatment with growth hormone or recombinant IGF-1. Patients may have been previously treated with growth hormone or IGF-1 therapy. If the patient is currently on one of these therapies, they will be required to discontinue treatment in order to begin the baseline observation period for this trial. That decision will be deferred to their treating clinical endocrinologists in conjunction with the patient's guardians. We anticipate that only patients who are having a poor response to their therapy will be interested in enrolling in the current study as there is no rationale for a patient who is receiving growth hormone therapy and having a positive response to enroll in the current study.
3. Prior treatment with a GnRH analog, aromatase inhibitor or oxandrolone
4. History of any type of malignancy
5. Chronic medical condition known to affect growth including but not limited to:
  - A. Cystic fibrosis
  - B. Diabetes
  - C. Inflammatory Bowel Disease
  - D. Celiac Disease
  - E. Asthma requiring a daily inhaled steroid dose > 400 micrograms of inhaled budesonide per day or equivalent
  - F. Taking daily oral glucocorticoids for any reason
  - G. Note – ADHD treated with a stimulant and treated hypothyroidism with a normal TSH will NOT exclude the subject from participating in the trial.
  - H. Turner Syndrome or any other chromosomal aneuploidy

- I. Congenital heart disease which places the subject at increased risk of an adverse cardiac outcome in the setting of hypotension including but not limited to: hypertrophic cardiomyopathy, aortic stenosis with peak gradient >50mmHg, severe aortic regurgitation (defined as pressure half time >500ms by echocardiogram), coronary insufficiency, or any anatomy with a need for an afterload reducing agent. Any patient with baseline abnormalities on echocardiogram will be reviewed with a pediatric cardiologist for appropriateness for inclusion in the study.
6. Malnutrition – Defined as a BMI <5th percentile (CDC growth charts)
7. Any clinically significant abnormality on screening tests as determined by the principal investigator. Abnormal screening labs may be repeated during the 6 month observation period prior to Day 1. If they return to normal or non-clinically significant deviations per the PI's determination, the subject may proceed with the study.
8. Known or suspected allergy to trial medication, excipients, or related products
9. The receipt of any investigational drug within 90 days prior to this trial

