### **Echocardiogram**

Cardiac anatomy and function will be evaluated by a standard 2-dimensional Doppler ECHO. The data recorded is to include ventricular cavity size, valve characterization (presence or absence of valve stenosis or regurgitation and clinical significance), ventricular wall thickness, regional wall motion, LV mass calculation, and pericardial characterization. Echocardiograms will be performed at the time points indicated in the Schedule of Activities (**Section 1.3**).

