### 9.2 SAMPLE SIZE DETERMINATION

This is an exploratory proof of principle Phase I/II study, and therefore, no formal sample size calculations were performed. The study size was chosen based on the feasibility of recruitment in this study time period.

Once the initial sample size of 35 subjects is achieved, we will discontinue recruitment of any genetic cohort with greater than 15 subjects. Additional recruitment efforts will then focus on achieving approximately 10 subjects in each of the cohorts.

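### Exclusion 5.I defines severe aortic regurgitation by a pressure half time above 500 ms, which contradicts the word severe and the purpose of the criterion, although other screening steps may still exclude a child with a large leak

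*Protocol*

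**What the plan says.** Exclusion 5.I in Protocol Section 5.2 bars "Congenital heart disease which places the subject at increased risk of an adverse cardiac outcome in the setting of hypotension". An open-ended list of examples follows. One of them is "severe aortic regurgitation (defined as pressure half time >500ms by echocardiogram"); its neighbour is "aortic stenosis with peak gradient >50mmHg". The half-time definition appears only here, and no other section of the protocol restates or corrects it.

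Three other provisions bear on the same child:

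- Item 5.I itself ends with a review step: "Any patient with baseline abnormalities on echocardiogram will be reviewed with a pediatric cardiologist for appropriateness for inclusion in the study".
- Item 7 of Section 5.2 excludes for "Any clinically significant abnormality on screening tests as determined by the principal investigator".
- Section 8.2 (Echocardiogram) has the echocardiogram report record "valve characterization (presence or absence of valve stenosis or regurgitation and clinical significance"). It does not list pressure half time among the data to be recorded.

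**The concern.** The parenthesis supplies the operative meaning of severe, and its inequality points away from severity. Pressure half time measures how quickly the aorta-to-ventricle pressure difference decays in diastole. A leak that is larger, all else equal, makes that decay faster and the half time shorter. A rule that selects long half times therefore selects slow decay.

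At stake is an eligibility threshold that serves safety. Rates of hypotension form part of the primary safety endpoint (Section 1.1), and hypotension events appear in the individual stopping and study suspension criteria (Section 7.1). Item 5.I is the exclusion that names hypotension as its reason. The extension phase applies none of the other exclusion criteria again (Section 5.2, Extension Phase Exclusion Criteria), so a classification made at screening is not revisited against this list.

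**Working it through.** The protocol has no calculation to reproduce on this point; Section 9.2 states that "no formal sample size calculations were performed", and an eligibility threshold would not enter one. The check is of direction.

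**1. Wording against wording.** In the neighbouring stenosis example a higher gradient is the worse finding, so a greater-than sign points toward severity. In the regurgitation example the same sign is attached to a measure that falls as the leak grows. The two examples stand in one list with one stated purpose, and only the second runs against it.

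**2. Direction from the meaning of the measure.** Take the aorta (compliance Ca) leaking into the ventricle (compliance Cv) through an orifice of area A, with pressure difference P.

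- Flow: Q = 50 × A × √P (mL/s, with A in cm² and P in mmHg).
- Decay: dP/dt = −Q × (1/Ca + 1/Cv).
- Solving for the time from P0 to P0/2: half time = 2 × √P0 × (1 − 1/√2) / [50 × A × (1/Ca + 1/Cv)].

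Half time is thus proportional to 1/A when P0, Ca and Cv are fixed.

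**3. Numbers.** None of these inputs is in the protocol; all are assumptions: P0 = 60 mmHg, Cv = 4 mL/mmHg, Ca from 0.5 to 2 mL/mmHg. For Ca = 1 and A = 0.1: 2 × 7.746 × 0.2929 / (50 × 0.1 × 1.25) = 4.537 / 6.25 = 0.726 s, or 726 ms.

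| Orifice area (cm²) | Ca = 0.5 | Ca = 1.0 | Ca = 2.0 |
|---|---|---|---|
| 0.02 | 2017 ms | 3630 ms | 6050 ms |
| 0.05 | 807 ms | 1452 ms | 2420 ms |
| 0.1 | 403 ms | 726 ms | 1210 ms |
| 0.2 | 202 ms | 363 ms | 605 ms |
| 0.3 | 134 ms | 242 ms | 403 ms |
| 0.4 | 101 ms | 182 ms | 303 ms |

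**4. Applying the written rule.** In every column, the entries above 500 ms are the smaller orifices and the entries below it the larger ones. The area at which the label changes moves with the assumption: two areas meet the definition at Ca = 0.5, three at Ca = 1.0 and four at Ca = 2.0. The order never changes.

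**5. What the table does not show.** A given half time does not fix a leak size: 0.4 cm² gives anything from 101 to 303 ms across the assumed compliances. The table supports a statement about direction and gives no basis for choosing a cut-off.

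**The case against.** The strongest reply is that item 5.I does not turn on the parenthesis. Its lead clause is mandatory and open-ended, so a child with a large leak who is at added risk under hypotension can be excluded whatever half time is measured. The same list also covers anatomy that calls for afterload reduction. The cardiology review, item 7 and the recorded clinical significance of regurgitation give further chances to stop that child. All of this stands.

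A reader might therefore infer too much in three ways:

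- **That the trial admits children with severe regurgitation.** The documents do not support this; such a child would have to pass every one of those layers.
- **That children with small leaks are being lost from rare cohorts.** This follows only if the parenthesis is applied mechanically against its own lead clause, and the protocol gives no count of such children.
- **That the Rasopathy cohort is especially exposed.** Item 5.I does not mention Rasopathies, and nothing in the protocol ties this definition to them.

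What does not stand is the further step that no correction is needed. The remaining safeguards are largely matters of judgement, exercised under a text that defines severe in the opposite sense, and none is written as a waiver for a child who meets a listed example. If staff follow the text, it misclassifies. If they recognise the slip and disregard it, decisions depart from the written criterion.

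**Conclusion.** The concern holds for the written definition. The parenthesis in exclusion 5.I contradicts both the word severe and the stated purpose of the criterion, and nothing else in the protocol corrects it. Within that one example the ordering is completely inverted: smaller leaks meet the definition and larger ones do not.

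The conclusion rests on what pressure half time measures, with starting gradient and compliances held fixed, and on no remembered guideline value. It does not extend to the screening process as a whole. The documents give no frequency of affected children, and none is claimed. No endpoint, analysis or statistical figure changes. The point merits correction because it concerns an eligibility threshold with a safety purpose in children, and the repair is small.

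**What to change.** The sponsor and the study cardiologist should reconcile the parenthetical definition in item 5.I, in both direction and value, with the word severe and with the purpose stated at the head of that item. The protocol offers no basis for a replacement cut-off, and none is proposed here.

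Existing screening echocardiograms and screen failures should then be checked against the reconciled wording.

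The cost is a one-line amendment and a review of existing reports. Because Section 8.2 does not list half time among the recorded data, some stored images may have to be re-read. No child needs a new procedure.

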#### Extension Phase Exclusion Criteria:

At the 12 Month Visit, the subject's bone age via the Greulich and Pyle method will not be greater than or equal to 13 years in females and 15 years in males. These patients have limited remaining growth potential.

None of the other exclusion criteria will be applied to the extension phase of the study as they would have been dealt with as adverse events during the trial.

### 5.3 LIFESTYLE CONSIDERATIONS

Not applicable

### 5.4 SCREEN FAILURES

Screen failures are defined as participants who consent to participate in the clinical trial but are not subsequently assigned to the study intervention or entered in the study. A minimal set of screen failure information is required to ensure transparent reporting of screen failure participants, to meet the Consolidated Standards of Reporting Trials (CONSORT) publishing requirements and to respond to queries from regulatory authorities. Minimal information includes demography, screen failure details, eligibility criteria, and any serious adverse event (SAE).

The most likely reasons for screen failures in this study are that the screening IGF-1 level done during the screening visit is below the normal range on our assay and a growth hormone stimulation test has not previously been performed. In those cases, the subjects will be referred back to their primary pediatric endocrinologist who can elect to perform a growth hormone stimulation test at their discretion. If the growth hormone stimulation test is performed and the subject meets study inclusion criteria after the results are available, the subject will then be deemed eligible for the study and will no longer be considered a screen failure. They will then continue with the protocol as scheduled.

### 5.5 STRATEGIES FOR RECRUITMENT AND RETENTION

Research subjects will be directly recruited at Children's National Hospital and will be referred to the study by pediatric endocrinologists and geneticists throughout the United States. Direct recruitment at Children's National will occur when members of the endocrinology or genetics division identify patients who meet the inclusion criteria. The study will be publicized throughout the United States in a number

of ways. First, the study will be listed on national websites including [clinicaltrials.gov](https://clinicaltrials.gov) as well as the Pediatric Endocrine Society website. Second, an email will be sent to the pediatric endocrinology list serve describing the study and providing information about how to refer to the study. Third, [name] (the PI) will publicize the study during presentations at national meetings and when he speaks at other institutions. Additionally, study brochures will be handed out at the annual Pediatric Endocrine Society meeting. Fourth, [name] will send direct emails to pediatric endocrinologists and geneticists throughout the US informing them about the study and providing information about how to refer eligible patients. All subjects will be recruited from within the United States.

Once a subject has been referred by their pediatric endocrinologist, we will then arrange for a telephone call to review the study details and confirm that the patient meets the inclusion and exclusion criteria. Prior to the telephone call, a copy of the consent forms will be provided to the family. During the telephone call, we will review all study procedures and answer any questions from the subject and their guardian(s). If, after the telephone call, the subject and guardian are interested in enrolling in the study, we will make arrangements for the screening visit which will also serve as the start of the observation period.

As the inclusion criteria are quite straightforward, we anticipate a small number of screen failures and estimate that we will screen up to 100 subjects to enroll the cohort of up to 75 subjects.

To enhance study retention, a minimum of monthly phone calls are scheduled once the intervention begins. We anticipate that subjects enrolled in this study will be highly motivated to complete the study and do not anticipate a high dropout rate.

The study will cover all travel costs for the subject and 1 parent including flights or mileage reimbursement for those who choose to drive, 2 nights in a hotel, transportation costs to and from the airport and to and from the hospital, as well as up to \$50 per person per day for meals. No additional incentives will be provided. We want to alleviate the financial burden of study participants but are not looking to incentivize subjects to participate in the study.

